# Study Schedule

Each eligible participant will be requested to visit the clinical site at enrollment and at each subsequent scheduled visit in accordance to the Schedule of Procedures (Appendix A). The evaluations that will occur at each visit are listed below.

## Screening Period (Day –28 to Day –7)

Informed consent will be obtained from all potential participants prior to initiation of any screening. The screening will be a two part process involving 1-2 visits. This process will be carried out in accordance with the guidelines for Good Clinical Practice (ICH E6) [4]. The consent process will be initiated by the CI or an appropriately qualified study person designated by the CI. Detailed instructions for obtaining and documenting informed consent of study subjects are outlined in section 14.3 Informed Consent Process.

After informed consent has been obtained, study eligibility will be assessed for each prospective participant. A complete medical history will be obtained (Appendix E) as well as a review of medication history including concomitant medications. A physical examination including measurement of vital signs will be performed as well as cardiac auscultation by a physician. A number of screening tests will also be performed. Please refer to appendix D for a comprehensive list of tests to be performed at screening. These tests include:

• Serum -HCG for all female participants;

• Routine hematology and biochemistry and urinalysis by dipstick test; (see Appendix D);

• Urine Drug Screen and alcohol breath test;

• Serum samples to be collected for ASOT, α-DNase B and α-J8 peptide antibodies;

• Throat swab and rapid antigen test for presence of Group A streptococcal infection

• Electrocardiogram (ECG) and echocardiogram (ECHO);

Participants who complete all screening procedures and satisfy all entry criteria will be considered eligible to participate in this study. To be eligible for study entry, clinical laboratory values at screening must not be clinically significant when outside the range of the normal values in the testing laboratory. Re-screening will not be allowed unless the CI considers the cause of the initial pre-screening failure to be of an acute and completely reversible nature.

If screening laboratory results are abnormal, e.g., HIV testing, the participant will be will be referred for appropriate counseling. If any clinically significant abnormalities are detected during screening, the participant will be referred for follow-up tests to a general practitioner or medical specialist as appropriate.

## Enrollment/Baseline

Participation consent must be obtained from all eligible participants prior to study product administration.

**Day 0, (Day of Dose 1)**

Two participants, one randomized to receive vaccine study product and the other control saline will have study product administered 24 hours prior to the remaining 18 participants which may be split into 2 cohorts. The safety of the first dose in these two participants will be initially observed for at least 6 hours and evaluated by the clinical investigator and the ISM to make recommendation on whether to proceed with administration of the study product to the remaining 18 participants.

These 2 participants will follow the events listed in Day 0 and will be dosed on Day 56 as all the participants of the study.

The safety of the first dose of the vaccine candidate in the study participants will be evaluated by a SMC that will make a recommendation to proceed to the administration of the next vaccine dose. See section 4 for the vaccine candidate dosage schedule. Refer to Appendix A for a tabular presentation of the study procedures.

Procedures to be followed at enrollment:

1. Review study eligibility and record concomitant medications.

2. Review medical history for any change in status from screening

3. Record baseline symptoms and vital signs. If the participant is febrile (temperature >38°C [>100.4F] or has an acute illness, the dose must be rescheduled. If rescheduled, the study product administration must be within 28 days after all screening procedures.

4. Targeted physical examination including cardiac auscultation. Particular attention to any elicited symptoms and signs consistent with rheumatic fever i.e. rash, arthalgia/arthritis (joint pain/swelling), renal angle tenderness and cardiovascular examination and movement disorder.

5. Obtain a throat swab and conduct a rapid antigen test for group A streptococci

6. Collect urine for urinalysis and blood for hematology, biochemistry and serology including, ASOT, α-DNase B, detection of α-J8 peptide vaccine specific antibodies, blood sample for quantitative cellular response as well as serum samples for α-DT antibodies and safety serum storage (refer to appendix D for tests required and blood volumes).

7. For female participants ensure that adequate contraceptive precautions have been taken since the screening pregnancy test and ensure that a urine test for -HCG is negative.

8. Perform breath alcohol test and urine drug screen.

9. Administer the study product.

10. Observe the first two sentinels, the first two participants for at least 6 hours after study product administration to evaluate for any adverse reactions.

11. For all other participants, observe for at least 30 minutes after study product administration to evaluate for immediate adverse reactions.

12. Repeat vital signs after minimum of 30 minutes after study product administration or at least before discharge. Record any immediate injection site reaction or systemic reactions if they occur.

13. Educate the participant during the post-study product administration waiting period on proper use of the thermometers and injection site reaction measurement aid. Discuss the signs and symptoms of potential adverse events (AEs) and review the instructions on completion of the memory aid.

14. Distribute Day 0-7 Memory Aid (MA).

## Treatment Period

The activities performed during the treatment procedures will be initiated by the investigators of the study or a qualified study person designated by the CI. Please refer to the table Appendix A for the activities that will occur at each of the scheduled visits.

**Day 2 ± 1 day (2 days after Dose 1, telephone call)**

1. Enquire for any acute complaints/adverse events/serious adverse events.

2. Review MA for solicited local and systemic reactogenicity and unsolicited events.

3. Review concomitant medications.

**Day 8 ± 2 (8 days after Dose 1, telephone call)**

1. Enquire for any acute complaints/adverse events/serious adverse events.

2. Review MA for solicited local and systemic reactogenicity and unsolicited events

3. Review concomitant medications.

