| **Description of Study Design:** | The purpose of this study is to evaluate the safety and immunogenicity of a Group A Streptococcus vaccine candidate. The participants (N=20) will be randomized 3:1 to receive the active intervention (N=15) or saline as placebo control (N=5). Participants randomized for intervention will receive either 50 µg of the vaccine candidate or saline. 2 participants will be dosed, 1 placebo and 1 investigational product 24 hours before the remaining 18 participants. They will be observed for 6 hours for any immediate adverse events. The ISM will review the data prior to the other 18 participants receiving study product. If no immediate serious adverse reactions have been observed the other 18 participants will receive an intramuscular injection of 0.5mL volume of the assigned study product. Safety of the first dose will be assessed by the Safety Monitoring Committee (SMC) before proceeding to administering the second dose to all 20 participants on Day 56. Clinical and adverse events/serious adverse event assessment will be conducted throughout the study at the scheduled clinic visits. Clinical specimens (urine and blood) will be collected from each participant to assess the safety and the immunogenicity of the investigational vaccine. Echocardiograms and electrocardiograms will be performed throughout the study to assess the safety of the vaccine formulation. |
| **Estimated Time to Complete Enrollment:** | The enrollment of all participants in this study will take approximately 4 weeks. |

**Schematic of Study Design**: Screening, Study Product Administration, Safety Testing, Safety Monitoring Committee Review for the cohort of 20 subjects

| **Vaccine Trial Schedule** | |
| --- | --- |
| **Time** (day) |  |
| Day -28 to Day -7 | Screening  ECG/ECHO/hematology/chemistry/urinalysis/ASOT/-DNAse B |
| Day 0^ | Dose 1 (n = 15A*, 5C*) |
| Day 8±2 | Memory aid completion |
|  |  |
| Day 28±7 | ECG/ECHO/hematology/chemistry/urinalysis/ASOT/-DNAse B |
| Day 35±5 | Database Collection of Data (up to Day 28 data) |
|  |  |
| Day 49±5 | SMC Dose 1 review |
| Day 56±5 | Dose 2 (n = 15A*, 5C*) |
| Day 64±2 | Memory aid completion |
|  |  |
| Day 84±7 | ECG/ECHO/hematology/chemistry/urinalysis/ASOT/-DNaseB |
| Day 98±5 | Database Collection of Data (up to Day 84 data) |
|  |  |
| Day 126±7 | SMC Dose 2 review |
|  |  |
| Day 180±14 | Follow up visit  Hematology/chemistry/urinalysis/ASOT/-DNAse B |
|  |  |

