A Memory Aid (MA) will be provided to participants to record their oral temperature, solicited and unsolicited symptoms, adverse events and concomitant medications. Each participant will be asked to record in memory aids the occurrence of any symptoms at the injection site (such as pain, tenderness, pruritis, erythema and induration) and systemic reactions such as fever, anorexia, nausea, malaise, myalgia, arthralgia and headache. Participants will also be asked to record any changes in urine that might suggest haematuria (blood-tinged or cola-coloured urine) and cutaneous abnormalities (rash or subcutaneous nodules). Information will be recorded daily for 7 days after each injection. Study personnel will review the information on the Memory Aid with the participant via phone calls (day 2 and 8 days after injection) to elicit as much information as possible about any reported symptoms. Based on this information, study staff will use his/her clinical judgment to assess the event and its severity and record the data on the Reactogenicity Record. Study staff will use the Reactogenicity Record to enter information into the database. The Memory Aid will not be collected from the participants.

All participants will be encouraged to contact clinical investigators or to visit the clinical site if they observe any grade 3 AE of the above mentioned reactions following each immunization.(see Appendix B), or if they have any concern. Adverse events and serious adverse events will also be reported at clinic visits throughout the study period.

Each participant will be required to visit the investigation site at the allocated days. Targeted physical examinations including cardiac auscultation by physician will be performed on day 28 after each vaccination and at follow-up visits on days 180, 266 and 350. Additional cardiac evaluation will include an electrocardiogram and transthoracic echocardiogram at day 28 following each injection and at the final follow-up visit on day 350. All study visits will be within the acceptable windows shown on Appendix A.

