**Day 28 ± 7 (28 days after Dose 1)**

1. Review medical history for any change in status from last study visit

2. Review any acute complaints/adverse events/serious adverse events.

3. Review concomitant medications.

4. Record vital signs.

5. Targeted physical examination including cardiac auscultation. Particular attention to any elicited symptoms and signs consistent with rheumatic fever i.e. rash, arthalgia/arthritis (joint pain/swelling), renal angle tenderness and cardiovascular examination and movement disorder.

6. Collect urine for urinalysis and blood for hematology, biochemistry and serology including ASOT, α-DNase B, detection of J8 vaccine specific antibodies and cellular responses and quantative cellular response.

7. Perform ECG and ECHO.

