**Day 64 + 2 (8 days after Dose 2, telephone call)**

1. Enquire for any acute complaints/adverse events/serious adverse events.

2. Review MA for solicited local and systemic reactogenicity and unsolicited events

3. Review concomitant medications.

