## Study Outcome Measures

The primary safety assessments will be based on the following outcomes:

• Solicited reactogenicity data acquired from a memory aid that will be kept for Days 0-7 following each product administration by each study participant.

- Local reactions following product administration include erythema (redness), induration (swelling), and pain, tenderness, and/or pruritis (itchiness) at the injection site.
- Systemic reactions following vaccination include feverishness, chills, diarrhea, anorexia (loss of apetite), vomiting, headache, malaise (feeling unwell), myalgia (muscle ache), nausea, rash, arthalgia/arthritis (joint pain/swelling), dyspnea (shortness of breath), wheezing, and abdominal pain.

• Participants will record their oral temperatures daily, as well as any changes that may suggest haematuria or cutaneous abnormalities

• Vital signs and a physical exam including organs targeted in rheumatic fever such as skin, joints, kidney and including cardiac auscultation will be acquired at each study visit.

• Clinical laboratory data acquired at four weeks post-study administration which include haematology, biochemistry, and urinalysis.

The secondary immunogenicity outcomes are based on the following outcomes:

• Production of peptide specific antibodies and increase in the titer for the specific antibodies from the baseline titer after product administration.

- The relationship between the doses administered and the titer of vaccine-specific antibodies

• The percent reduction in a bactericidal assay of group A streptococcus colony forming units (CFU) that elicited vaccine specific antibodies.

- The percent reduction in a bactericidal assay of group A streptococcus CFU achieved in M1, M6 and 88/30 (Australian clinical isolate) group A streptococcus strains

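### The last memory aid review after Dose 1 may fall on Day 6 or 7, before the Day 0-7 record is complete, and the protocol gives two different windows for the same call after Dose 2

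*Protocol*

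**What the plan says.** Section 11.5 (Study Outcome Measures) lists first among the primary safety outcomes: "Solicited reactogenicity data acquired from a memory aid that will be kept for Days 0-7 following each product administration by each study participant". The diary is handed out on the day of Dose 1 in Section 7.2 ("Distribute Day 0-7 Memory Aid (MA"), and Section 7.3 repeats this at Dose 2.

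Section 4 (Study Design) describes how the diary becomes data. Staff go through it with the participant by telephone about 2 and 8 days after each injection, judge the severity of each event and complete a Reactogenicity Record. The database is filled from that record. Section 4 adds: "The Memory Aid will not be collected from the participants".

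Section 7.3 gives the timing of the second call after Dose 1 as "Day 8 ± 2 (8 days after Dose 1, telephone call", with the task "Review MA for solicited local and systemic reactogenicity and unsolicited events". The next scheduled contact is "Day 28 ± 7 (28 days after Dose 1". Its procedures include an adverse event enquiry but no review of the memory aid, and the same is true of the Day 56 visit.

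For Dose 2, Section 7.3 gives "Day 64 + 2 (8 days after Dose 2, telephone call", while the Vaccine Trial Schedule in the Protocol Summary gives "Day 64±2 | Memory aid completion".

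**The concern.** The call that closes the diary should not be allowed to happen before the diary ends. With a symmetric window, a site can telephone on Day 6 or Day 7, be fully compliant, and record an incomplete solicited period. The participant goes on filling in the aid, but no scheduled step then brings the remaining entries into the Reactogenicity Record.

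This touches the first-listed primary safety outcome, which is also part of the data package for the Safety Monitoring Committee (Sections 11.4 and 11.9.1). Section 11.9.1 reports the maximum grade per participant for each reaction type, and missing days act on a maximum in one direction only. The Dose 2 discrepancy adds to this: one wording removes the problem after the second injection and the other repeats it, so staff cannot tell which applies.

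**Working it through.** The plan states no figure to reproduce here. The check is window arithmetic and a comparison of passages.

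**Inputs**
- Last diary day: Day 7 (Sections 7.2 and 11.5).
- Final review call after Dose 1: Day 8 ± 2 (Section 7.3, and the same window in the Protocol Summary schedule).
- Final review call after Dose 2: Day 64 + 2 (Section 7.3) or Day 64 ± 2 (Protocol Summary schedule), with Dose 2 nominally on Day 56.
- Next scheduled contact after the Dose 1 call: Day 28 ± 7 (Section 7.3).

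**1. Dose 1.** The window runs from 8 − 2 = 6 to 8 + 2 = 10, so the permitted days are 6, 7, 8, 9 and 10. Days 6 and 7 fall on or before the last diary day: 2 of 5.
- A call on Day 6 misses all of Day 7 and whatever happens on Day 6 after the call.
- A call on Day 7 misses the rest of Day 7.

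So at most one full diary day and part of another are absent.

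**2. Dose 2, given on Day 56.**

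| Source | Study days | Days after dose | Permitted days on or before diary Day 7 |
|---|---|---|---|
| Section 7.3 (+2) | 64 to 66 | 8 to 10 | 0 of 3 |
| Protocol Summary schedule (±2) | 62 to 66 | 6 to 10 | 2 of 5 |

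The two sources disagree on whether an early call is allowed.

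**3. Whether a later step picks up the missing entries.** The Day 28 visit falls on Days 28 − 7 = 21 to 28 + 7 = 35. That is 21 − 7 = 14 to 35 − 7 = 28 days after the last diary day. It asks about adverse events but lists no memory aid review, and Day 56 lists none either. The early termination visit (Section 7.6) reviews the aid only where this has not already been done. The aid stays with the participant (Section 4).

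**4. Direction of effect.** A participant's maximum grade over Days 0 to 7 is at least as high as the maximum over the shorter period seen at an early call. The recorded value is therefore equal to or below the complete one. It differs only if a reaction first appears, or first reaches its peak, after the call.

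**5. After the change.** Day 8 + 2 gives Days 8 to 10, and no permitted day falls on or before Day 7.

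**The case against.** The strongest reply is that an early call does not lose the event.
- Section 9.2.1 asks participants to report any event arising after the diary review, at a visit or by telephone, and requires onset, severity and changes in severity to be recorded. Section 8.1 has all adverse events assessed at every visit. A late reaction raised at Day 28 would still be graded.
- Solicited data do not come from the telephone alone. Section 8.1 has staff examine the injection site immediately before and after each dose and assess systemic symptoms 30 minutes after it.

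This stands, and it limits the point to the contemporaneous daily record for the last one to two days.

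A reader might go further and infer that a halting rule could be missed. The 10% rules in Section 9.5 use the same 7 days, and at full enrolment 10% of 20 is 2 participants, so a single unrecorded grade 3 reaction could in principle matter. The documents do not support treating this as an established failure. Sections 4 and 8.1 encourage participants to contact or visit the site for grade 3 reactions, and that route does not depend on the Day 8 call.

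It can also be said that not collecting the aid is deliberate: Section 4 treats it as a prompt for an interview and makes the Reactogenicity Record the graded record. This stands too. Section 12 does list participant diaries among source documents, but as a general definition that neither names the memory aid nor requires its collection. A reader might infer that the graded data cannot be verified. That is too broad: database entries can be checked against the Reactogenicity Record. What cannot be checked is that record against the participant's own entries.

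Finally, the lone plus sign in the Dose 2 heading may be a typing or text-conversion slip, since the schedule gives ±2 for both doses. That is a reason to reconcile the two places, not to leave them.

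**Conclusion.** The point holds as a data-capture defect of modest size. After Dose 1, two of the five permitted call days precede completion of the diary. A call on either day leaves up to the last one to two days of contemporaneous graded solicited data out of the Reactogenicity Record, and any effect on the maximum grade is downward or nil. After Dose 2 the same gap exists or not, depending on which of two conflicting windows governs.

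This assumes that the last diary entry is Day 7, that windows count whole days from the injection, and that Appendix A, which Section 4 names for visit windows and which is not in the text at hand, does not settle the matter differently.

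Two larger readings are tempting and are not supported.
- **A quantified loss.** Counting Days 6 and 7 as 2 of 8 daily entries gives 25%, but Day 6 would be only partly missed. One vaccinee in 15 is 6.7 percentage points, but that holds for any single missed event and says nothing about how often this window causes one. The documents give no rate of early calls or of late-onset reactions.
- **A distorted comparison between doses.** Different windows after the two doses are not established, because the protocol disagrees with itself on the second. Section 11.6 plans only descriptive statistics. Study assessors are blinded (Section 5.3.2), so nothing points to differential loss by arm either.

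**What to change.** Set the final memory aid review call at 8 days after each dose with a +2 window only, and state that it is not made before the Day 7 entry is complete. Align the Day 8 and Day 64 headings in Section 7.3, the Vaccine Trial Schedule in the Protocol Summary, and Appendix A.

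Count the window from the actual injection, as the Section 7.3 headings already imply. Dose 2 may be given on Day 56 ± 5, so a fixed Day 64 could lie anywhere from 64 − 61 = 3 to 64 − 51 = 13 days after it.

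The cost is a few words and a narrower call window for site staff: three permitted days in place of five.

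As an optional extra, the completed aids could be collected at the existing Day 28 and Day 84 visits and compared with the Reactogenicity Record. That is 20 participants × 2 doses = 40 aids and no new visit. It would reverse an explicit choice in Section 4 and is not needed to correct the window.

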**Day 28 ± 7 (28 days after Dose 1)**

1. Review medical history for any change in status from last study visit

2. Review any acute complaints/adverse events/serious adverse events.

3. Review concomitant medications.

4. Record vital signs.

5. Targeted physical examination including cardiac auscultation. Particular attention to any elicited symptoms and signs consistent with rheumatic fever i.e. rash, arthalgia/arthritis (joint pain/swelling), renal angle tenderness and cardiovascular examination and movement disorder.

6. Collect urine for urinalysis and blood for hematology, biochemistry and serology including ASOT, α-DNase B, detection of J8 vaccine specific antibodies and cellular responses and quantative cellular response.

7. Perform ECG and ECHO.

**Day 56 ± 5 (Day of Dose 2)**

1. Ensure that an approval has been granted from SMC to proceed with the second study product administration.

2. Review inclusion/exclusion criteria.

3. Review medical history for any change in status from last study visit.

4. Review any acute complaints/adverse events/serious adverse events.

5. Review concomitant medications. If the participant has received an antibiotic treatment within 14 days prior to this administration, at discretion of the CI the participant may be withdrawn from the study or the administration of the second dose rescheduled within the allowed window for administration of the dose.

6. Record baseline symptoms and vital signs. If the participant is febrile (temperature >38°C [>100.4F] or has an acute illness, the study product administration must be rescheduled within the allowed window for administration of the dose.

7. Obtain a throat swab and conduct a rapid antigen test for group A streptococci.

8. Obtain a urine sample from all female participants for -HCG testing. Ensure that the testing is negative before study product administration.

9. Perform breath alcohol test and urine drug screen.

10. Collect urine for urinalysis and blood for hematology, biochemistry and serology including, ASOT, α-DNase B and detection of α-J8 peptide vaccine specific antibodies and blood sample for quantitative cellular response as well as serum samples for α-DT antibodies and safety serum storage (refer to appendix D for tests required and blood volumes).

11. Targeted physical examination including cardiac auscultation. Particular attention to any elicited symptoms and signs consistent with rheumatic fever i.e. rash, arthalgia/arthritis (joint pain/swelling), renal angle tenderness and cardiovascular examination and movement disorder.

12. Administer the study product in the alternate arm from previous dose.

13. Observe for at least 30 minutes after study product administration to evaluate for immediate adverse reactions. Repeat vital signs after approximately of 30 minutes after study product administration, or at least prior to discharge. Record any immediate injection site reaction or systemic reactions if they occur.

14. Educate the participant during the post-study product administration waiting period on proper use of the thermometers and injection site reaction measurement aid. Discuss the signs and symptoms of potential adverse events (AEs).

15. Distribute Day 0-7 post second study product administration MA and review the instructions on completion of the memory aid.

